#### Health Related Quality of Life

The EuroQol is a widely-used standardised measure of self reported health [41] using questions in five domains (EQ-5D) that is applicable to a wide range of health conditions and treatments providing a simple descriptive profile and a single index value for health. ***Pain*** is measured by a numeric rating scale (NRS) (0-10) [42]. The Charnley's Hip Score as used in the SAHFE protocol (Standardized Audit of Hip Fractures in Europe) is used as a supplement [43].

#### Gait

Gait assessments are recorded for a subset of participants being able to walk without assistance from another person and attending the 4- and/or 12-month evaluations at the outpatient clinic. These measurements are performed using an electronic gait mat GaitRite^® ^which is regarded a reliable measure of spatio-temporal gait parameters also in elderly and frail people [44-46]. Participants should preferably walk the gait mat without walking aids. ***Physical activity ***is monitored in all patients when sensors are available for use. For these measurements we are using the small body worn accelerometer-based sensor ActivPal^®^[47], which is undergoing extensive evaluation in our research group [48].

#### Falls and fear of falling

Number of falls and fall related injuries are registered retrospectively in three ways at each follow-up; through medical records, and asking the patient and the next of kin. Fear of falling is assessed by a) asking a simple question: "Are you afraid of falling"-yes/no scored on a simple four-point Likert scale [49] and b) by applying the 7-item Falls Efficacy Scale International (FES-I) [50].

***Cognitive function ***is measured by use of the Clinical Dementia Rating scale (CDR)[51] based on registrations from next of kin and the performance based screening tool of patients, the Mini Mental State Examinations (MMSE)[52].

#### Depression

To assess the effect of the intervention on depressive symptoms we use the Geriatric Depression Scale 15 (GDS-15) [53-55]. GDS-15 can be interpreted as an indication of presence/absence of depressive mood [56,57].

#### Health economics

We will compare direct costs related to treatment in the orthogeriatric ward vs orthopedic ward, readmissions, rehabilitation, care in institutions, and home care services by calculating the incremental cost effectiveness ratio (ICER) and use a non-parametric bootstrapping approach. We will assign a value to the EuroQol states using previously developed tariffs of values. Robustness of results to choice of value set will be discussed. Where there are incomplete (censored) benefits or cost data due to loss to follow-up we will use non-parametric methods to infer cumulative costs and benefits [58,59]. Information on time of death will be collected from the National Registry.

#### Hospital related information

Data on cause and duration of any hospital admissions during the trial period is extracted from participants' hospital records. Hospital records will also be the most important information source for medication, previous and present co-morbidity and data related to pre-, peri- and postoperative monitoring.

#### Consent and enrolment

Nurses on call in the Emergency Department will undertake eligibility screening of all hip fracture patients. If there is a free bed in the orthogeriatric unit patients fulfilling the inclusion criteria are informed about the study and asked to participate. Depending on general health, pain, anxiety and fatigue study information is given as a short version. Proxies are informed about the study when appropriate and/or available, especially in relation to patients whose consenting competence could be questioned. Written consent is collected primarily at admittance in the Emergency Department or occasionally on day 3 or 5 at the clinical ward where research assistants routinely give a second orally, and also a written version of the study information to be kept by the patient or proxy. Furthermore, participating patients consent to participation for all four data collection points, otherwise being excluded. Explicit oral consent is accepted for patients unable of writing. At each data collection point participants receive repeated information on the study.

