### Intervention

Patients randomised to the intervention group are transferred directly from the Emergency Department to the orthogeriatric ward while control patients are transferred to the trauma unit at Department of Orthopaedic Surgery. Orthopaedic surgeons are responsible for the initial assessment, diagnosing of the fracture and decisions on type of surgery for both groups. Anaesthesiologists make preoperative assessments regarding analgesia, operability and perioperative anaesthesiological procedures. After surgery and for a limited time period all patients are observed in the recovery unit.

On request orthopaedic surgeons examine study patients in the orthogeriatric ward and supervise the staff. Geriatricians serve the orthopaedic ward equivalently.

The experimental intervention program is offered only during the acute hospital stay. The orthopaedic surgeons decide on traditional follow-up consultations after discharge irrespective of group allocation.

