#### Randomisation and allocation concealment

After giving their informed consent participants are enrolled and randomized to immediate transfer for medical treatment in the orthogeriatric unit followed by surgical treatment by orthopaedics and further geriatric work-up and management in the orthogeriatric unit, or to receive traditional care in the Department of Orthopaedics. Randomisation is performed by using a web-based computerised randomisation service at the Unit of Applied Clinical Research, NTNU. Randomisation is blocked, with a random block length being integrated into the programming.

Research assistants are monitoring all hip fracture patients admitted to the hospital. Occasionally eligible patients may mistakenly be transferred to the Orthopaedic Department without being evaluated for eligibility. If not already being transferred for immediate surgical treatment and within 24 hours since admittance, patients are informed about the study and asked to participate. If patients consent, they are enrolled and randomised according to the protocol. After surgical treatment these patients are transferred to the orthogeriatric unit or returning to the orthopaedic unit according to results of the randomisation.

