#### Data collection

For practical reasons it is not possible to implement systematic blinding of testing during the hospital stay. For the 1-, 4-, and 12-month assessments testers will not have access to information about the patients' group assignment.

Background information on living conditions, physical and cognitive function before the fracture is collected for all participants starting already during the stay in the Emergency Department. On day 3 or 5 research assistants collect details from patients' on falls history, use of mobility aids, pre-fracture scoring of Barthel ADL-Index and Nottingham extended I-ADL Scale when the clinical condition makes it appropriate, or from proxies when they are available. These registrations will be used as explanatory variables in the statistical analyses.

Mobilisation is monitored using CAS during the 3 first days after the operation. On day 3 a research assistant attaches an ActivPal sensor anteriorly on the non-affected thigh for at least a 24-hour activity monitoring. The sensor is removed on day 5. On day 5 or the nearest working day a SPPB mobility score is completed by a research assistant.

Research assistants will continually scrutinise study forms on missing data. Missing data from proxies are collected through telephone calls, as is also information needed to fill in the CDR form. Electronic hospital records will give further information on clinical examinations, medication, blood tests and other investigations performed during the index stay.

The 1-month registration is performed by research assistants at the site where the patient is living, irrespective of location. This might be the patient's own home, a nursing facility or a rehabilitation institution. The time window is 4 weeks ± 5 days. For details on data collection and questionnaires, see Table 1. Information on Barthel ADL Index or Nottingham extended I-ADL Scale items are collected primarily from the patients depending of cognitive function, or alternatively from the proxy. Whenever possible, information on participants living at remote locations from St. Olav Hospital is collected by trained local physiotherapists hired as research assistants.

**Table 1 T1:** Measures, scales, questionnaires and time-points of data collection

Index stay	1 month postoperatively	4 and 12 months postoperatively
CAS (3 days)		
SPPB	SPPB	SPPB
TUG	TUG	TUG
	Place of residence	Place of residence
	MMSE	MMSE
	GDS-15	GDS-15
	FES-I	FES-I
	EQ-5D	EQ-5D

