### Power and statistical analyses

Sample size estimates are based on mobility assessed by SPPB at 4 months following the fracture. A change in the SPPB score of 0.5 points is considered a small but meaningful change, while 1 point is considered a more substantial change. In order to detect an effect size of 1.0 when power is 80% and alpha = 0.05, a sample size of 304 participants would be needed. Based on data from a previous prospective observational study in a similar study population (work in progress), we expect a drop out rate of 10% due to death and 10% due to withdrawals during the first 4 months following the fracture. To allow for 304 patients to remain in the project at four months after the fracture 380 persons need to be included. Thus, the plan is to include a total sample of 400 participants. The assumptions underlying the sample size (i.e. the standard deviation at baseline) has been checked by an independent clinical trials unit after the first 200 patients enrolled, and found to be acceptable.

All data will be analysed and presented according to the updated CONSORT guidelines for reporting parallel group trials[60]. Patterns of missing data will be explored prior to analysis, and accounted for in the analysis by imputation methods [61]. To study differences in change between groups we will use multivariate analyses by use of mixed models for longitudinal data by general linear modelling (GLM) for continuous outcomes and by logistic regression for binary outcomes [62]. To study associations between the new clinical pathway and time to events, we will use Kaplan Meyer plots and the Cox proportional hazards regression model. In all analyses we will control for confounding factors and interactions and present both unadjusted and adjusted effects with 95% confidence intervals.

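### As written, the all-four-data-points consent rule permits exclusion of already randomised patients on day 3 or 5, when their ward is known

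*Protocol article*

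**What the plan says.** All references are to the protocol article.

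- Consent and enrolment, on timing: "Written consent is collected primarily at admittance in the Emergency Department or occasionally on day 3 or 5 at the clinical ward". At that ward contact research assistants routinely repeat the study information orally and hand over a written version. The information given in the Emergency Department may have been abbreviated, depending on the patient's condition.
- Consent and enrolment, on the condition attached to consent: "participating patients consent to participation for all four data collection points, otherwise being excluded". By Table 1 the four points are the index stay and 1, 4 and 12 months.
- Consent and enrolment, on oral consent: "Explicit oral consent is accepted for patients unable of writing".
- Randomisation and allocation concealment, on the order of events: "After giving their informed consent participants are enrolled and randomized to immediate transfer". For patients missed at admission: "If not already being transferred for immediate surgical treatment and within 24 hours since admittance, patients are informed about the study and asked to participate".
- Intervention: "Patients randomised to the intervention group are transferred directly from the Emergency Department to the orthogeriatric ward", while controls go to the trauma unit.
- Data collection: "it is not possible to implement systematic blinding of testing during the hospital stay".

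**The concern.** The exclusion rule has participating patients as its subject and stands shortly after the sentence that allows a signature on day 3 or 5. Nothing limits it to the time before allocation. If a patient who hears the fuller information on the ward will not agree to every data point, the text allows that patient to be excluded. By then the patient, the proxy and the research assistant can all see which ward the patient is in.

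Willingness to continue at that moment may depend on the ward, its staff and early recovery. If it does, and refusers leave the analysis, the groups compared at 4 months are no longer the groups that were randomised. The article does not say whether exclusion means from the trial, from follow-up or from the analysis. Its plan for missing data does not say whether an excluded patient counts as missing or drops out of the denominator.

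**Working it through.** **1. Order of events.** Patients are randomised in the Emergency Department, for immediate transfer. The only later route into the trial is open within 24 hours of admittance and before surgery. Day 3 and day 5 lie beyond both limits, so a consent form signed then belongs to a patient already randomised. The arms are in different wards, so allocation is evident.

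**2. Reach of the rule.** Two readings fit the text.
- *Entry condition:* all four points must be accepted before randomisation. No randomised patient is lost.
- *Continuing condition:* it also applies when the form is signed on the ward. A refusal then excludes a randomised patient with allocation known.

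The text does not choose between them. Nor does it say what consent a day 3 or 5 signer gave earlier, since oral consent is mentioned only for patients who cannot write.

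**3. The plan's own figures.** Power and statistical analyses states: "In order to detect an effect size of 1.0 when power is 80% and alpha = 0.05, a sample size of 304 participants would be needed". It expects 10% deaths and 10% withdrawals by 4 months: 304 / (1 − 0.20) = 380, which reproduces the article's figure. The SD behind 304 is not given. With 152 per arm, a difference of 1.0 SPPB point, two-sided alpha 0.05 (sidedness is assumed) and 80% power:

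SD = √(152/2) × 1.0 / (1.960 + 0.842) = 8.718 / 2.802 = 3.11.

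Read as a standardised effect, 1.0 would need only 32 patients in total, so a 1-point difference is the sensible reading.

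**4. Loss of power.** Assume that all 401 were randomised, a share e is excluded after randomisation, 20% are lost later, and SD = 3.11. Evaluable N = 401 × (1 − e) × 0.80.

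| e (assumed) | Evaluable N | Power for 1.0 point |
|---|---|---|
| 0% | 320.8 | 82.1% |
| 2% | 314.4 | 81.3% |
| 5% | 304.8 | 80.1% |
| 10% | 288.7 | 78.0% |

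**5. Bias.** Let R be the mean 4-month SPPB of retained patients in an arm, e the share excluded, and d the amount by which excluded patients fall below those retained. The mean of the whole randomised arm is (1 − e) × R + e × (R − d) = R − e × d. Analysing only the retained patients overstates that arm by e × d. If both arms lose patients with the same d, e is the excess in one arm. The article gives neither e nor d, so both are assumed.

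| Excess e | d = 2 | d = 3 |
|---|---|---|
| 2% | 0.04 | 0.06 |
| 5% | 0.10 | 0.15 |
| 10% | 0.20 | 0.30 |

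The range is 0.04 to 0.30 point, or 4% to 30% of the 1.0-point target. The top value is 60% of the 0.5 point that the article regards as a small change that still matters (0.30 / 0.50). With equal shares excluded and equal d in both arms, the bias in the difference is zero.

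**The case against.** The strongest reply is that the condition belongs to enrolment. It stands under a heading about consent and enrolment, and the randomisation section puts informed consent before allocation, for ordinary and late-found patients alike. The ward contact is described as routine repeat information, not as a second eligibility check. On that view, consent comes first, the signature occasionally later, and no randomised patient is lost. This reading is possible and may be the intended one. It is not stated, however, and it leaves open what happens to a patient who declines to sign on day 3 or 5.

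Three stronger inferences are tempting, and the article does not support them:

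- *That randomised patients were removed selectively.* Late signing is called occasional, no number of exclusions is given, and nothing shows a difference by arm.
- *That the consent and randomisation sections contradict each other.* Informed consent before randomisation and a signature afterwards can both be true. What is missing is a description of the earlier consent.
- *That randomised patients who decline the 12-month visit lose their 4-month SPPB.* No passage says so. The article plans for withdrawals, imputation and mixed models, and the flowchart legend expresses attrition relative to those allocated.

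The size is also fairly challenged. A 10% excess is about 20 of 200 patients in one arm, a great many to arise from an occasional practice, so the upper end is an extreme. Finally, an analysis-set definition may well stand in an analysis plan that is not shown, and its absence here is no fault. The point is about an exclusion rule that the article does state.

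**Conclusion.** The point holds as a defect in a stated rule, not as evidence of bias. Applied to patients who sign on day 3 or 5, the rule excludes after randomisation with allocation known, and the text permits that application. Whether it happened, and whether it happened unequally, cannot be told from the article. The 401 are reported as having consented, which does not settle whether anyone randomised was later dropped.

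The matter at stake is bias rather than numbers. The 0.04 to 0.30 point rests entirely on the assumed excess and deficit. Near the lower end it is negligible, and it is zero if the rule was used only before allocation. Power stays between 82.1% and 78.0% for 0% to 10% excluded. This should be fixed before analysis, but it does not invalidate the design.

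**What to change.** 1. State that the all-four condition applies only before randomisation, and what form of consent preceded randomisation for patients who signed on day 3 or 5.
2. Keep every randomised patient in the analysis set of the allocated arm.
3. Treat refusal on day 3 or 5, or of a later data point, as full or partial withdrawal. Use all data for which consent was not refused, and handle the rest as missing under the planned methods.
4. Report by arm how many written consents came after randomisation and how many were refused. The promised CONSORT reporting gives this a natural place.

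The cost is a clarifying sentence, an analysis-set definition (if the analysis plan does not already have one) and a short table. The downside is that some retained patients will have incomplete data. The change can still be made without knowledge of results: the article says that analysis had not begun, and that only the study statistician will be unmasked before final follow-up is complete. Offering consent separately for each data point at entry is no longer possible, because recruitment has ended.

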#### Randomisation and allocation concealment

After giving their informed consent participants are enrolled and randomized to immediate transfer for medical treatment in the orthogeriatric unit followed by surgical treatment by orthopaedics and further geriatric work-up and management in the orthogeriatric unit, or to receive traditional care in the Department of Orthopaedics. Randomisation is performed by using a web-based computerised randomisation service at the Unit of Applied Clinical Research, NTNU. Randomisation is blocked, with a random block length being integrated into the programming.

Research assistants are monitoring all hip fracture patients admitted to the hospital. Occasionally eligible patients may mistakenly be transferred to the Orthopaedic Department without being evaluated for eligibility. If not already being transferred for immediate surgical treatment and within 24 hours since admittance, patients are informed about the study and asked to participate. If patients consent, they are enrolled and randomised according to the protocol. After surgical treatment these patients are transferred to the orthogeriatric unit or returning to the orthopaedic unit according to results of the randomisation.

#### Data collection

For practical reasons it is not possible to implement systematic blinding of testing during the hospital stay. For the 1-, 4-, and 12-month assessments testers will not have access to information about the patients' group assignment.

Background information on living conditions, physical and cognitive function before the fracture is collected for all participants starting already during the stay in the Emergency Department. On day 3 or 5 research assistants collect details from patients' on falls history, use of mobility aids, pre-fracture scoring of Barthel ADL-Index and Nottingham extended I-ADL Scale when the clinical condition makes it appropriate, or from proxies when they are available. These registrations will be used as explanatory variables in the statistical analyses.

Mobilisation is monitored using CAS during the 3 first days after the operation. On day 3 a research assistant attaches an ActivPal sensor anteriorly on the non-affected thigh for at least a 24-hour activity monitoring. The sensor is removed on day 5. On day 5 or the nearest working day a SPPB mobility score is completed by a research assistant.

Research assistants will continually scrutinise study forms on missing data. Missing data from proxies are collected through telephone calls, as is also information needed to fill in the CDR form. Electronic hospital records will give further information on clinical examinations, medication, blood tests and other investigations performed during the index stay.

The 1-month registration is performed by research assistants at the site where the patient is living, irrespective of location. This might be the patient's own home, a nursing facility or a rehabilitation institution. The time window is 4 weeks ± 5 days. For details on data collection and questionnaires, see Table 1. Information on Barthel ADL Index or Nottingham extended I-ADL Scale items are collected primarily from the patients depending of cognitive function, or alternatively from the proxy. Whenever possible, information on participants living at remote locations from St. Olav Hospital is collected by trained local physiotherapists hired as research assistants.

**Table 1 T1:** Measures, scales, questionnaires and time-points of data collection

Index stay	1 month postoperatively	4 and 12 months postoperatively
CAS (3 days)		
SPPB	SPPB	SPPB
TUG	TUG	TUG
	Place of residence	Place of residence
	MMSE	MMSE
	GDS-15	GDS-15
	FES-I	FES-I
	EQ-5D	EQ-5D
	NRS-pain	NRS-pain
ActivPal (24 hours)		ActivPal (4 days)
		GaitRite
Hand grip strength	Hand grip strength	Hand grip strength
		Quadriceps strength
Before fracture:		
Barthel Index	Barthel Index	Barthel Index
NEIADL	NEIADL	NEIADL
Falls	Falls	Falls
Walking aids	Walking aids	Walking aids
CDR	CDR	CDR

Abbreviations: CAS = Cumulative Ambulation score, CDR = Clinical Dementia Rating, EQ-5D = EuroQual-5 Domains, FES-I = Falls Efficacy Scale-International, GDS-15 = Geriatric Depression Scale, MMSE = Mini Mental State Examination, NEIADL = Nottingham extended Instrumental Activities of Daily Living, NRS = Numeric Rating Scale, SPPB = Short Physical Performance Battery, TUG = Timed Up & Go.

The 4-month registration is performed by a research assistant at the hospital out-patient facility applying the present infrastructure for testing aspects of mobility and gait using the electronic gait mat. To secure maximal study compliance and low attrition rate, transportation both to and fro is taken care of by the same experienced taxi driver. An ActivPal sensor is worn for at least a 96-hour period of activity monitoring. Participants are urged to be tested at the hospital. In case of extensively impaired physical or mental capacity a pragmatic and reduced test protocol is applied in their own home or where they are staying for the time being. The time window is 4 months ± 2 weeks. For details on data collection and questionnaires, see Table 1.

The 12-month registration is performed similar to the 4-month registration. The time window is 12 months ± 4 weeks. For details on data collection and questionnaires, see Table 1.

